## Statistical Analysis

The aim of the analysis is not to definitively demonstrate efficacy in this early phase trial. Rather the data will be used to inform a decision on whether or not to undertake subsequent studies of UP. Assuming a normal distribution, independent t-tests will be used to compare groups between trial arms for follow-up measures, together with 95% confidence intervals to inform preliminary conclusions on clinical benefit. Within-group analysis will be assessed using paired t-tests. If a normal distribution cannot be assumed, analogous non-parametric methods will be used.

Associations between potential prognostic indicators and the ability to pedal will be examined using Fishers Exact test.

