### Measurement battery

Baseline measures will be made before randomisation and outcome measures after the intervention phase has been completed (figure 1). Baseline measures consist of two sets: prognostic indicators and clinical efficacy. Outcome measures will consist of clinical efficacy measures only.

The ***participant characteristics ***to be recorded for all potential participants and participants will be: gender, age (years), type and site of the stroke lesion (liaison with medical team from scanning/clinical findings) and time since stroke onset at entry to the trial and at each set of study measures (days).

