##### Primary outcome

1. Ability to voluntarily contract paretic muscle

This will be measured by the Motricity Index (MI) lower limb section [35]. The MI is a widely used measure and has established validity and reliability for use after stroke [37]. It is an ordinal weighted scale with six measurement levels within each of three categories for the lower limb. The three categories are: ankle dorsiflexion, knee extension, and hip flexion. For each movement, a score of 0, 9, 14, 19, 25, or 33 is given, where 0 is no movement, 19 is full range movement against gravity not against resistance and 33 is normal power.

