#### Prognostic indicator measures

5. Site of stroke lesion

The location and size of stroke lesion have been demonstrated to be a prognostic factor for functional outcomes after stroke [28,29]. It is possible, therefore, that this clinical factor might be linked to the ability to take part in rehabilitation interventions. Brain lesion location will therefore be recorded from the clinical scan.

6. Degree of muscle weakness as measured by the Motricity Index (see clinical efficacy measures)

7. Ambulatory Capacity as measured by the Functional Ambulatory Categories (see clinical efficacy measures)

The FAC has been found to have good predictive validity for community ambulation after stroke (FAC ≥ 4 predicts community ambulation at six months with 100% sensitivity and 78% specificity) [38]. It is proposed that pedalling exercise might have a positive effect on walking and thus postulated that the ability to walk might influence the ability to pedal and respond to pedalling intervention.

8. Ability to control the trunk

As measured by the Trunk Control Test [37]. This is a short, simple measure of motor loss developed for use after stroke. Patients are asked to do four movements-rolling to their weak side, rolling to their strong side, sitting up from lying down and balancing in a sitting position. Each movement is scored according to ability, either 0, 12 or 25, leading to a total score out of 100. Validity and reliability (comparison with Rivermead Motor Assessment at six, twelve and eighteen weeks post-stroke-Spearman's rho, *r*= 0.70, 0.72 and 0.79 respectively; interrater reliability, Spearman's rho, *r = *0.76, p < 0.001) have been established [37].

Balance (trunk) control is highly specific to ambulatory control, and makes a crucial contribution to the ability to perform activities of daily living [41]. The Trunk Control Test has been found to be a predictor of functional outcomes after stroke, including significant correlation with: discharge Functional Independence Measure (Pearson's *r *= 0.738) and gait velocity (Pearson's *r *= 0.654) [31]; and discharge walking ability (Spearman's rho = 0.71) [36]. It is possible, therefore, that trunk control early after stroke might influence the ability to perform rehabilitation activities and thus will be assessed as a potential prognostic indicator for pedalling exercise after stroke.

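### The between-arm comparison of follow-up Motricity Index leaves out the baseline score already collected, which gives up precision and leaves a small trial exposed to chance imbalance

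*Protocol article*

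**What the plan says.** The Statistical Analysis section fixes the comparison between arms: "independent t-tests will be used to compare groups between trial arms for follow-up measures, together with 95% confidence intervals". It adds that "Within-group analysis will be assessed using paired t-tests" and gives one fallback: "If a normal distribution cannot be assumed, analogous non-parametric methods will be used". None of these sentences brings the baseline value, or a change score, into the comparison between arms, and no other section does so.

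The primary outcome is the ability to contract paretic muscle: "This will be measured by the Motricity Index (MI) lower limb section". The Measurement battery section states that "Baseline measures will be made before randomisation and outcome measures after the intervention phase has been completed" and that "Baseline measures consist of two sets: prognostic indicators and clinical efficacy". MI belongs to the clinical efficacy set. It is also listed under Prognostic indicator measures: "Degree of muscle weakness as measured by the Motricity Index (see clinical efficacy measures". Every randomised participant should therefore have a baseline MI before allocation.

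The Study procedure section describes randomisation in blocks of four and mentions no stratification. The Sample Size section sets 24 participants from expected recruitment, without a power calculation. The intervals are meant for use: the plan speaks of "95% confidence intervals to inform preliminary conclusions on clinical benefit" and of informing the decision on further studies.

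**The concern.** A comparison of follow-up scores alone treats the differences between participants at entry as noise. Entry runs from 3 to 30 days after stroke, so starting MI may vary a good deal. If baseline MI predicts MI about two weeks later, part of that noise can be removed with data already in hand. With so few participants, the two arms can also differ at baseline by chance, and an unadjusted estimate carries part of that difference.

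The within-group tests raise a second issue. Both arms receive conventional therapy in a period that the Background section describes as favourable to neurological recovery. Improvement is therefore expected in both arms whether or not pedalling adds anything. A paired test in the pedalling arm measures total change, not the effect of pedalling.

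What is at stake is the quality of the estimate and interval that inform whether larger trials go ahead. The sample size is fixed by recruitment, so precision has to come from the analysis.

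**Working it through.** **The plan's own figure.** Two participants per month × 12 months = 24, as the Sample Size section states. There is no power figure to reproduce.

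**Inputs.** 24 randomised in blocks of four gives 12 per arm. This is the best case: the abstract places the 24 before the attempt to pedal, and only those able to pedal are randomised. The 95% level is from the Statistical Analysis section. The baseline to follow-up correlation *r* is not given anywhere, so 0.3 to 0.8 is assumed. All results are in units of the follow-up SD and assume roughly normal scores with equal SDs.

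**1. Half-width of the planned interval.**
t(0.975, 22) × √(2/12) = 2.074 × 0.408 = 0.85 SD.

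**2. Half-width with baseline MI in the model.**
t(0.975, 21) × √(2/12) × √[(1 − r²)(1 + 1/20)]. The factor 1 + 1/20 allows for estimating the slope (24 − 4 = 20).

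| r (assumed) | Half-width, SD | Narrower than 0.85 by |
|---|---|---|
| 0.3 | 0.83 | 2% |
| 0.5 | 0.75 | 11% |
| 0.7 | 0.62 | 27% |
| 0.8 | 0.52 | 38% |

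Setting the two formulas equal gives a break-even at r ≈ 0.23. At r = 0 the adjusted half-width would be 2.080 × 0.408 × √1.05 = 0.87 SD, so the most that adjustment can lose is about 3%.

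On the large-sample variance ratio, 24 participants with adjustment are worth 24/(1 − r²) without it: about 26 at r = 0.3, 32 at 0.5, 47 at 0.7 and 67 at 0.8.

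**3. Chance baseline imbalance.**
The SD of the difference in baseline means is √(2/12) = 0.408 SD. The probability of a difference of 0.4 SD or more in either direction is 2 × [1 − Φ(0.4/0.408)] = 0.33. Given a difference of size δ, the unadjusted follow-up difference shifts by r × δ on average: 0.7 × 0.4 = 0.28 SD.

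**4. Within-group tests with no effect of pedalling, 12 per arm.**
The SD of change is √[2(1 − r)]. If both arms gain 0.5 SD and r = 0.7, the standardised change is 0.5/√0.6 = 0.65, and each paired test is significant with probability 53% (noncentral t, 11 df). The pattern of a significant pedalling arm beside a non-significant control arm then has probability 0.532 × 0.468 = 25%. A between-arm test wrongly favours pedalling with probability 2.5%. The size of the gain is also assumed: with a gain of 0.25 SD, each paired test is significant with probability 14% to 42% for r from 0.6 to 0.9; with a gain of 1.0 SD, 94% or more.

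**The case against.** **The t-test is not wrong.** A reader might infer that the planned comparison is biased or has an inflated error rate. It does not: over all possible randomisations it is unbiased and keeps its 5% level. The loss is in precision, and in how far the one trial that is run can be moved by its own allocation. Nor does an imbalance pass undiminished into the result; only the fraction *r* of it does.

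**The gain rests on a correlation that the document does not give.** The protocol says that MI predicts walking outcomes, not how well MI predicts later MI. Entry is limited to Functional Ambulation Categories 0 to 2 and then to those able to pedal, and both limits could lower *r*. At r = 0.3 the gain is about 2%. This stands: the interval is materially wider than necessary only if the correlation is moderate or high.

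**The paired tests have no stated role in judging efficacy.** The plan attaches its conclusions on benefit to the between-arm comparison and its intervals. It would be tempting to say that natural recovery will make the paired tests positive and that the trial will read this as benefit. Neither follows from the text: the amount of recovery is unknown, and no use of these tests is stated. What remains is that they cannot isolate the effect of pedalling.

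**This is an early-phase study with other inputs to the decision.** The Aims section sets several efficacy measures against pain and fatigue, so the MI interval is not the sole basis. This lowers the weight of the point without answering it, because MI is the primary outcome and the change is almost free.

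**The fallback for non-normal data.** One might add that a rank test leaves no interval, or that the ordinal walking scale is badly served. The fallback permits rank methods, which can supply an interval, and the rule for switching may be left to an analysis plan. Neither is pressed here.

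**Conclusion.** The point holds as one of efficiency and of exposure to chance imbalance, not of validity. The article names its between-arm method and leaves out a baseline score that it collects; this is a stated choice, not a detail deferred to another document. The omission is certain from the text, but the size of the loss is not: it runs from negligible at r = 0.3 to more than a third of the interval's width at r = 0.8. The imbalance probability of about 33% needs no correlation, only 12 per arm and approximate normality, and it rises if fewer are randomised. The paired tests should carry no weight in judging efficacy, although the document does not say that they will.

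**What to change.** State that the between-arm analysis of MI is a linear model of follow-up MI on arm and baseline MI, reporting the adjusted difference with its 95% CI. Use the value from the second baseline set, taken after the participant has shown an ability to pedal and before allocation. As the safeguard against non-normality, name a baseline-adjusted rank-based or permutation analysis, so that the fallback also uses the baseline. Report change within each arm descriptively, and say that it will not be used to judge efficacy.

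The cost is one degree of freedom (22 to 21 at 12 per arm) and a few words in the analysis section. No new data, visits or participants are needed. If the correlation proves to be near zero, the interval widens by about 3% at most.

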#### Study procedure

All participants will undergo baseline measurement set 1 (prognostic indicators). They will then be assessed for their ability to perform UP. Potential participants will be taken to the treatment area and shown the cycling equipment. If content to proceed, a hoist will be used to seat them on the bike safely. They will be asked to pedal slowly for one minute to familiarise themselves with the equipment. They will then be asked to pedal for one further minute and a visual observation of whether they can pedal or not will be made.

Those unable to pedal and who are 31 days or more after stroke onset will be excluded from the randomised part of this trial. Those unable to pedal and who are 30 days or less after stroke onset will be offered further pedalling assessments approximately every three days. The rationale for further pedalling assessments is that, during the first 30 days after stroke, people may experience fear of movement or emotional distress and therefore may need more than one experience of pedalling within a therapeutic environment. Without repeated opportunities for pedalling assessment some participants may be excluded unfairly from the opportunity to participate in UP.

Those participants able to pedal for one minute and who are 30 days or less after stroke onset, will then undertake baseline measures set 2 (clinical efficacy). Participants will then be allocated randomly to either routine conventional physical therapy (CPT; control group) or to CPT plus UP (experimental group). Randomisation order will be generated before the trial begins by an independent statistician, in blocks of four. Group allocation will be concealed in sequentially numbered opaque sealed envelopes held by an independent administrator, who is not involved in the study and will have no contact with study participants. The next highest number envelope will be opened by the independent administrator in response to a telephone request from the research therapist. After opening, envelopes will be stored securely with the participants' study data. Randomisation will be concealed from the independent outcome assessor and participants will be asked not to discuss group allocation with the outcome assessor.

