### Participant inclusion criteria and recruitment process

Participants will be recruited from an acute stroke unit and, if necessary due to pressure on stroke beds, medical wards; in a University Hospital Trust. Consultant and therapy teams have agreed to support this trial.

Stroke survivors will initially be approached by a clinical team member responsible for their care, to check that they agree to speak to a researcher. If they agree, then a researcher will provide potential participants with verbal and written printed information about the trial. A video of the procedure for getting on and off the exercise cycle will also be available if patients wish to view it. A minimum of twenty four hours (1 working day) later, informed, signed consent will be sought. Those providing written informed consent will be participants in this trial. All potential participants will then be screened to check that they meet the study criteria, which are;

• adults aged 18+

• three to thirty days following a unilateral stroke resulting in unilateral muscle weakness with or without sensory deficit;

• fit to participate as assessed by a consultant-led medical team with resting oxygen saturations 95% or above, resting heart rate 90 beats per minute or less and systolic blood pressure of 100-160 mmHg

• score 0, 1 or 2 on the Functional Ambulation Categories [32]. Clinically, this means unable to walk; or need the help of two or more people; or require firm continuous or intermittent support of one person assisting with weight and balance;

• be able to sit unsupported for 30-seconds on the edge of a bed with feet on the floor.

• have sat out of bed in a chair or wheelchair at least once for a continual period of 15-minutes i.e. have appropriate sitting tolerance to participate in this cycling intervention;

• be able to follow a one-stage command i.e. sufficient communication, orientation and memory to participate in this cycling intervention;

• be independently mobile with or without an aid prior to the index stroke;

• have no co-existing pathology contributing to observed impairment in the paretic lower limb e.g osteoarthritis with associated knee deformity.

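### The walking outcome (FAC) is compared without adjustment although a prognostic baseline Trunk Control Test is already collected in everyone, so some precision on a secondary outcome is given up

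*Protocol article*

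**What the plan says.** The Statistical Analysis section of the protocol article fixes the between-arm method: "independent t-tests will be used to compare groups between trial arms for follow-up measures". Interval estimates are to accompany these tests and to guide early judgements of benefit. The fallback reads "If a normal distribution cannot be assumed, analogous non-parametric methods will be used". Neither sentence gives a covariate. FAC at follow-up is secondary outcome 2 and serves Aim 1d, so it falls under this rule.

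Under Study procedure, "All participants will undergo baseline measurement set 1 (prognostic indicators") before the pedalling assessment and before randomisation. The Trunk Control Test, scored out of 100, belongs to that set. Under Prognostic indicator measures the article cites its correlation with "discharge walking ability (Spearman's rho = 0.71") as a reason for including it. Its only planned use is in this sentence: "Associations between potential prognostic indicators and the ability to pedal will be examined using Fishers Exact test".

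On entry, participants must "score 0, 1 or 2 on the Functional Ambulation Categories" and must be able to sit unsupported for 30 seconds.

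**The concern.** The article argues that trunk control predicts later walking and measures it in everyone before allocation, then leaves it out of the one between-arm comparison of walking. A pre-randomisation covariate that predicts the outcome can be adjusted for without introducing bias and makes the interval for the arm difference narrower.

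Precision matters here because the confidence intervals are the stated output. They are meant to inform the decision on further trials, and the Discussion considers not proceeding if efficacy is not shown. The FAC is the measure chosen to represent activity-level change. Randomisation is described as blocks of four with no stratification factor named, so nothing described in the design balances trunk control between the arms.

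**Working it through.** **The plan's own figure.** Sample Size gives two participants per month over 12 months: 2 × 12 = 24. This reproduces. It is a recruitment figure; the article gives no power, effect size or standard deviation.

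**Inputs.**
- From the article: total of 24; two arms in blocks of four; 95% intervals; cited correlation 0.71.
- Assumed: 1:1 allocation (no ratio is stated); correlation r between the Trunk Control Test and follow-up FAC from 0.2 to 0.71; randomised numbers N of 24, 16 and 12, because the Abstract sends only those able to pedal into the randomised trial.

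**Formulas**, in units of the outcome SD, with n = N/2 per arm:
- Unadjusted half-width = t(0.975, N − 2) × √(2/n).
- Variance ratio, adjusted to unadjusted = (1 − r²) × (1 + 1/(N − 4)). The second factor is the expected cost of chance covariate imbalance.
- Adjusted half-width = t(0.975, N − 3) × √(2/n × variance ratio).

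**N = 24.** The unadjusted half-width is 2.074 × √(2/12) = 0.847. For r = 0.4 the variance ratio is 0.840 × 1.05 = 0.882, and the half-width is 2.080 × √(0.882/6) = 0.797.

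| r | 1 − r² | Variance ratio | Half-width (SD) | Change |
|---|---|---|---|---|
| 0.2 | 0.960 | 1.008 | 0.852 | 1% wider |
| 0.3 | 0.910 | 0.956 | 0.830 | 2% narrower |
| 0.4 | 0.840 | 0.882 | 0.797 | 6% narrower |
| 0.5 | 0.750 | 0.788 | 0.753 | 11% narrower |
| 0.6 | 0.640 | 0.672 | 0.696 | 18% narrower |
| 0.71 | 0.496 | 0.521 | 0.613 | 28% narrower |

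**Fewer randomised.** At N = 16 the interval narrows by 4% (r = 0.4), 9% (0.5) and 26% (0.71). At N = 12 the figures are 1%, 7% and 24%.

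**Break-even r**, where the adjusted and unadjusted half-widths are equal: about 0.23 (N = 24), 0.30 (N = 16) and 0.37 (N = 12). If a second covariate that explains nothing is added, these become about 0.33, 0.42 and 0.52.

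**Narrowed range.** Let u be the SD of the Trunk Control Test in this trial divided by its SD in the cited cohort (unknown, so assumed). Then r′ = r·u / √(1 − r² + r²u²), starting from r = 0.71:

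| u | r′ | Variance ratio (N = 24) | Interval narrower by |
|---|---|---|---|
| 0.8 | 0.63 | 0.64 | 20% |
| 0.6 | 0.52 | 0.77 | 12% |
| 0.4 | 0.37 | 0.90 | 5% |

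**Check on an ordinal score.** A simulation cut a latent normal variable into six levels (assumed cut-points), with 12 per arm and one covariate. Rejection under no effect was about 5% for the t-test, the Mann-Whitney test and ANCOVA. With an assumed shift of 0.8 SD, the mean half-width went from 1.26 to 1.24 FAC levels at a latent correlation of 0.3, to 1.13 at 0.5, and to 0.94 at 0.724. These agree with the formula to within a few percentage points.

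**The case against.** **This is efficiency, not error.** A two-sample comparison after randomisation is valid. Chance imbalance in trunk control (SD √(2/12) = 0.41 SD at 12 per arm, or 0.41 × 0.71 = 0.29 SD in the outcome at the highest r) is already inside the unadjusted standard error. It is the same lost precision seen from another side and should not be counted as a further harm. This stands in full.

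**The stakes are modest.** FAC is secondary, the trial disclaims definitive proof of efficacy, and the Discussion says interpretation will reflect the small sample. This stands, and it limits the weight of the point.

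**The correlation may not transfer.** A reader might infer from 0.71 that adjustment would halve the variance and be worth doubling the trial. The article does not support that. The value is a Spearman coefficient from a cited cohort, for walking at discharge and not for FAC after up to ten working days. The sitting requirement overlaps with one of the four Trunk Control Test items, and the FAC 0–2 and able-to-pedal conditions select further. Entry is possible from day 3 and pedalling can be reassessed to day 30, so unless the test is repeated a value could be up to 27 days old at randomisation. All of this stands; 28% is a ceiling.

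**Adding baseline FAC could cancel the gain.** Baseline FAC takes only three adjacent values, so it may explain little, although the article has no data on this. If it explains nothing, the break-even figures with two covariates show that the gain is small at N = 24 and can vanish or reverse at 16 or fewer when r is near 0.4. This stands, and it argues for one covariate.

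**It could be left to an analysis plan.** This does not stand. The article itself names an unadjusted test; it is not silent on the method.

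**Conclusion.** The point holds as an efficiency improvement to a secondary outcome. Nothing in the article makes the planned FAC comparison biased or invalid, and a reader should not take the missing adjustment as either.

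If 24 are randomised and the correlation in this sample is 0.4 to 0.5, the plan gives up about 6% to 11% of interval width. The loss reaches about 28% only if 0.71 applies unchanged, which is unlikely. If markedly fewer are randomised the gain shrinks, and below the break-even correlations adjustment costs slightly more than it returns.

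The size rests on an assumed correlation, 1:1 allocation and treating the FAC score as roughly linear. None of these can be checked from the article.

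**What to change.** In Statistical Analysis, before unblinding, make the main FAC comparison a model with arm and the set 1 Trunk Control Test total as the single covariate: ANCOVA on the score, or an ordinal or rank-based equivalent. Report the adjusted difference with its 95% confidence interval, and keep the unadjusted comparison as a check. Add baseline FAC only if the number randomised supports a second covariate, and write that condition down in advance.

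The cost is a sentence in the plan and a few lines of code, with no new data and no burden on participants. Statistically it costs one degree of freedom, with no return if the correlation falls below the break-even values. Record the days between the Trunk Control Test and randomisation in the report, so that readers can judge how old the covariate was.

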**Discussion:**

This protocol is for a trial of a novel therapy intervention. Findings will establish whether there is sufficient evidence of benefit to justify proceeding with further research into clinical efficacy of upright pedalling exercise early after stroke. Information on potential prognostic indicators will suggest which stroke survivors could benefit from the intervention.

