## Aims

The driver for this proposed research is the hypothesis that UniCam crank-assisted upright pedalling (UP), used as an adjunct to conventional physical therapy, enhances recovery of lower limb motor function in stroke survivors with substantial paresis early after stroke. However, before this hypothesis can be tested in a phase III trial, it is important to establish whether there is sufficient evidence of benefit (clinical efficacy) to justify proceeding to subsequent larger trials and which stroke survivors are most likely to be able to participate in UP (prognostic indicators). Therefore, the aims for the current early phase clinical research study are:

1. Clinical Efficacy

To determine whether there is sufficient evidence for UP, balancing efficacy and potential adverse events (pain and fatigue), to justify proceeding to subsequent larger clinical trials; as assessed by:

a) ability to voluntarily contract paretic muscle;

b) production of reciprocal activation of antagonistic muscle groups during pedalling, similar to walking;

c) timing of onset and offset of activity in antagonist muscle groups during pedalling, similar to walking;

d) ability to walk independently.

2. Prognostic Indicators

To determine whether site of stroke lesion, trunk control ability, severity of lower limb paresis and/or ambulatory ability predicts ability to use UP within 30 days of stroke onset.

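### Aim 2 fixes Fisher's exact test for ordered scores: valid, but with 24 people it gives up much of the power a rank test would keep, and entry day is left unadjusted

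*Protocol article*

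**What the plan says.** The Statistical Analysis section gives one method for the second aim: "Associations between potential prognostic indicators and the ability to pedal will be examined using Fishers Exact test". It names no categories or cut-points. The non-parametric fallback in the same section belongs to the t-tests for the trial comparison and comes before this sentence.

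The four indicators are:

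- **Motricity Index, leg.** For each of three movements "a score of 0, 9, 14, 19, 25, or 33 is given".
- **Trunk Control Test.** Four movements, each scored on three levels, "leading to a total score out of 100".
- **FAC.** Described as ordinal under Secondary outcomes, and limited to 0, 1 or 2 by the inclusion criteria.
- **Lesion site.** Nominal, from the clinical scan.

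The outcome is binary: "a visual observation of whether they can pedal or not will be made". Under Study procedure, people who fail and are still within 30 days "will be offered further pedalling assessments approximately every three days". The indicators are taken before the first attempt, and no repeat measurement is stated. Aim 2 asks whether the indicators, among them "ambulatory ability predicts ability to use UP within 30 days of stroke onset", so the natural outcome is ability at any assessment up to day 30. Entry is allowed from day 3 to day 30. Time since onset is recorded (Measurement battery) but does not appear in the analysis.

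The Abstract's Discussion paragraph adds: "Information on potential prognostic indicators will suggest which stroke survivors could benefit from the intervention".

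**The concern.** For three of the four indicators the question is whether higher scores go with being able to pedal. Fisher's test does not use that ordering. A score with many possible values must either be cut, at a point the plan does not give, or spread over columns holding one or two people each. Both waste information, and 24 people leave none to spare.

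The costly error is a false finding that nothing predicts ability to pedal. The Discussion section says that if no indicator is linked to pedalling, larger trials using the current indicators can be avoided. An inefficient test makes that reading more likely when a predictor does exist.

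A second matter affects the same analysis. People who enter early have more chances to be classed as able than people who enter late, and the analysis has no term for this. If scores are related to entry day, the association with ability by day 30 mixes the two.

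**Working it through.** **Sample size.** Two recruits per month × 12 months = 24, which reproduces the stated figure. No power is stated for Aim 2. No significance level is given either; 0.05 two-sided is assumed here, in keeping with the 95% intervals.

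**1. Smallest attainable p-values.** With 24 people split 12/12 at the median and k unable to pedal, perfect separation puts all k in the lower half. The two-sided Fisher p is 2 × C(12,k)/C(24,k). For the exact rank-sum test without ties it is 2/C(24,k).

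| Unable | Fisher, 12/12 split | Rank-sum |
|---|---|---|
| 2 | 132/276 = 0.48 | 2/276 = 0.007 |
| 3 | 440/2024 = 0.22 | 2/2024 = 0.001 |
| 4 | 990/10626 = 0.093 | 2/10626 = 0.0002 |
| 5 | 1584/42504 = 0.037 | 2/42504 = 0.00005 |

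A median-split Fisher test therefore cannot reach 0.05 unless at least five people cannot pedal.

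**2. Power, simple model.** Normal scores in the two groups, shifted by √2 × z(0.80) = 1.414 × 0.842 = 1.19 SD, which gives an AUC of 0.80. Results are by simulation and vary by one or two points between runs.

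| Unable / able | Fisher, median split | Exact Mann-Whitney | Difference (points) |
|---|---|---|---|
| 6 / 18 | 29% | 62% | 33 |
| 8 / 16 | 49% | 71% | 22 |
| 12 / 12 | 59% | 77% | 18 |

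**3. Power, second model.** Discrete scores are noisy readings of one latent severity (loading 0.8), with an odds ratio of 3 or 5 per latent SD and 50%, 70% or 85% able to pedal. Motricity Index:

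| Odds ratio | Method | 50% able | 70% able | 85% able |
|---|---|---|---|---|
| 3 | Fisher, median split | 26% | 21% | 6% |
| 3 | Fisher, raw scores | 10% | 5% | 2% |
| 3 | Rank-sum | 47% | 43% | 28% |
| 5 | Fisher, median split | 45% | 35% | 11% |
| 5 | Fisher, raw scores | 14% | 11% | 4% |
| 5 | Rank-sum | 73% | 66% | 45% |

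Leaving the scores uncut does not rescue Fisher's test. For FAC on its three levels the loss is about 4 to 11 points (for example 25% against 30% at odds ratio 3 with 50% able). For lesion site there is none.

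**4. Number of attempts.** Entering on day d and reassessed every three days to day 30, a person has at most 1 + floor((30 − d)/3) attempts: 10 for day 3, 7 for day 12, 4 for day 21, and 1 for days 28 to 30.

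**5. Does this bias the associations?** Entry spread over days 3-30, ability by day 30 as outcome, no true association, and an assumed correlation between score and entry day:

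| Correlation | Odds ratio per SD (truth 1) | Rejection rate, Fisher | Rejection rate, rank-sum |
|---|---|---|---|
| 0 | 0.99 | 2.1% | 4.3% |
| 0.3 | 0.83 | 2.3% | 6.0% |
| −0.3 | 1.20 | 2.1% | 6.3% |
| 0.6 | 0.69 | 4.8% | 12.1% |

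If all entry falls on days 3-14, the null odds ratio stays between 0.90 and 1.04. With first-attempt ability as outcome it is about 1.0 at every correlation tried.

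**The case against.** The strongest reply is that this is a declared early-phase study. No power calculation is claimed, and the Discussion section says interpretation will reflect the small sample. Fisher's test keeps its error rate, so no false positive is threatened. Much of the low power comes from having 24 people: at an AUC of 0.70 even Mann-Whitney has only about 29-38% power with 6 to 12 unable. All of this stands. It limits the point to inefficiency, but it does not argue for keeping the less efficient test.

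A reader might infer that unequal numbers of attempts do distort the associations. The documents do not support that. It requires ability by day 30 as the outcome and a relation between score and entry day, and no figure for such a relation is given. It is plausible, since scores taken later may reflect recovery, but with no correlation there is no bias. One might also calculate that, with a 30% chance of success at each independent attempt, 97% of day-3 entrants but 30% of day-30 entrants would end as able. That assumes away persistent weakness and is an illustration only.

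A reader might also conclude that the first attempt should become the main outcome. That would conflict with Aim 2's 30-day window. It would also cut across the stated reason for reassessment, that fear or distress early after stroke may hide ability.

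Finally, an analysis plan that is not shown could supply cut-points. It would not remove the loss, because Fisher's test itself is fixed here.

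**Conclusion.** The point holds as a nearly cost-free improvement, not as an error that invalidates the aim. Fisher's exact test is valid for all four indicators and suitable for lesion site. For the Motricity Index and Trunk Control Test it gives up roughly 18 to 33 points of power after a median split at an AUC of 0.80, and it has no chance of significance with four or fewer unable under a 12/12 split. For FAC the loss is modest. The AUC, the odds ratios, the number unable and the median split are all assumptions, since the documents give none of them.

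The dependence of attempts on entry day is real and unaddressed. Confounding from it is possible, not shown. It does bear on the remedy: on the unadjusted 30-day outcome the rank-sum rejection rate rises to about 12% at a correlation of 0.6, so the change of test and the adjustment for entry day belong together.

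The Abstract's statement about who could benefit goes beyond Aim 2, which relates indicators only to the ability to pedal.

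**What to change.** 1. Use exact Mann-Whitney tests, with AUC and 95% confidence interval, for the Motricity Index and Trunk Control Test. Use an exact trend or rank test for FAC. Keep Fisher's exact test for lesion site.
2. Keep ability to pedal within 30 days as the Aim 2 outcome and say so in the analysis section. Stratify or adjust for days since stroke at entry, for example with a stratified rank test or with exact or penalised logistic regression, and report the number of attempts per person.
3. Report first-attempt ability as a sensitivity analysis.
4. Reword the Abstract so that the indicators inform who can take part, not who benefits.

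This is a change of wording and analysis only. Days since stroke is already recorded, and the indicators and pedalling verdicts are already collected. The reassessment schedule is untouched. The price is that with 24 people the adjustment must be simple, such as two or three entry-day bands, and it will use up some of the power gained.
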